## 6.2 Duration of intervention

The LHW intervention will be implemented over eighteen months. As new patients are enrolled in the clinic, their permission will be requested for referral to a LHW for an initial home visit. LHW will conduct a standardised assessment and describe the support and referrals provided through the project; new families enrolled in the study clinics will be visited following the same schedule as clinic appointments, namely once a fortnight for the first month, every 4 weeks in the following 2 months, and subsequently every 3-months. Children who are not yet eligible for ART will receive the same schedule of home visits, to encourage retention in care during the routine monitoring phase. Once they become eligible and initiate ART, the first 3 home visits will be repeated to deliver the activities related directly to treatment issues.

## 6.3 Monitoring and Evaluation of the intervention

In addition to the outcome evaluation comparing retention rates and clinical results between the intervention and control arms of the study, a process evaluation will be conducted during the LHW programme implementation. A monitoring and evaluation framework (see Appendix 18.5) will be developed during finalisation of the intervention design, and is likely to include documentation of activities (ease of recruiting LHW, completion rates for training, retention in programme, geographical coverage); compilation of routine statistics (client load per LHW, frequency of household visits, service mix provided, accompanied visits to health facilities); qualitative data collection to assess the quality of programme delivery (interviews with LHW, participatory evaluation exercises for client households, interviews with enrolled family members); and recording and analysis of any external events that could influence the intervention’s ability to achieve its aims (political instability, adverse weather conditions or catastrophic events, changes in relevant health or social policies).

# HIV CLINICAL COHORT IN PHC

## 7.1 Eligible participants

Children aged 6-15 years who are test HIV positive at the seven study clinics and reside in Harare will be eligible for recruitment into the cohort study, regardless of whether they are eligible for recruitment into the randomised trial. Patients aged 6-15 years who are already on ART and accessing care at a secondary health facility will be offered HIV care at the study PHC they attend, but will not be eligible for recruitment into the cohort study.

## 7.2 Cohort study data collection

Patients who test HIV positive and choose to register for HIV care at the PHC will be invited for an initial assessment within a week of diagnosis. The assessment will include:

- Record of social history: Current household structure, family history, type of guardianship, knowledge of HIV status, schooling
- Review of clinical history: HIV testing history, past infections including TB, other significant illness, hospitalisations, HIV testing history
- Clinical assessment: standardised symptom screen, WHO clinical stage
- Examination: standardised clinical examination, growth assessment, lung function assessment
- Tests: CD4 count, blood sample store

Patients will be referred for counselling and started on cotrimoxazole prophylaxis, and followed up two weeks later for assessment of ART eligibility (according to National Guidelines).

Those who are not eligible for ART will be followed up a month after the initial assessment, and then on a three monthly basis. At each visit, patients will have a brief symptom screen and undergo measurement of height and weight. Cotrimoxazole will be given and patients will have brief counselling. If participants start ART during the follow-up period, they will require an additional visit 2 and 4 weeks later, before reverting back to their follow-up schedule.

Those who are eligible for ART will be referred for counselling and started on the recommended first-line treatment. They will be then followed up at 2 weeks, and then monthly for 2 months and three monthly thereafter. At each visit, they will have a brief symptom screen, assessment of adherence, and measurement of height and weight. ART dose will be checked at each visit and adjusted according to weight.

For all participants, a CD4 count, growth and lung function assessment will be performed every 6 months, and psychosocial assessment (knowledge of HIV diagnosis, guardianship, schooling, disclosure to others) and pubertal staging carried out annually.

Participants who miss scheduled appointments will be offered alternative appointments for clinical review at the next available date. All participants will be followed up for 72 weeks. Participants recruited earlier in the study will continue to receive 3 monthly cohort follow-up until the study ends. At the end of the follow-up period, all participants will continue to receive their routine HIV care at the respective PHCs.

## 7.3 PHC Patients not enrolled in cohort study

Patients who register for HIV care at the PHC, but decline consent to participation into the cohort study will be receive the same level of care as participants enrolled into the clinical cohort. However, the following will not be carried out:

- Assessment of lung function
- Detailed growth and pubertal staging
- Viral load testing one year after starting ART
- Blood sampling for immunogenetic studies
- Detailed psychosocial and adherence assessment

## 7.4 Follow-up Schedule of cohort

**Table 7.1 Follow-up schedule for cohort participants who are not yet on ART**

|  | **Week** | | | | | | | | | | |
| --- | --- | --- | --- | --- | --- | --- | --- | --- | --- | --- | --- |
| **0** | **2** | **4** | **8** | **12** | **24** | **36** | **48** | **60** | **72** |  |
| Nurse visit1 |  |  |  |  |  |  |  |  |  |  |  |
| Weight/Height |  |  |  |  |  |  |  |  |  |  |  |
| HC, MUAC2 |  |  |  |  |  |  |  |  |  |  |  |
| Lung function testing |  |  |  |  |  |  |  |  |  |  |  |
| T-cell subsets |  |  |  |  |  |  |  |  |  |  |  |
| Blood sample store |  |  |  |  |  |  |  |  |  |  |  |
| Psychosocial assessment3 |  |  |  |  |  |  |  |  |  |  |  |
| Pubertal Staging4 |  |  |  |  |  |  |  |  |  |  |  |
| Referral for TB investigations (if TB symptoms)5 |  |  |  |  |  |  |  |  |  |  |  |

1Symptom checklist, hospitalisation, new diagnoses

2HC-head circumference; MUAC- mid-upper arm circumference;

3Knowledge of diagnosis, disclosure to others, schooling, guardianship, family HIV test

4For children aged 9 years or older

5Sputum (expectorated or induced), CXR, stool, urine will be collected as part of a collaborative study to be conducted by [name] (see Appendix 18.10)

**Table 7.2 Follow-up schedule for cohort participants who start ART**

|  |  | **Week** | | | | | | | | | | |
| --- | --- | --- | --- | --- | --- | --- | --- | --- | --- | --- | --- | --- |
| **0** | **2** | **4** | **6** | **8** | **12** | **24** | **36** | **48** | **60** | **72** |  |
| Start ART |  |  |  |  |  |  |  |  |  |  |  |  |
| Nurse visit/collect medication1 |  |  |  |  |  |  |  |  |  |  |  |  |
| Weight/Height |  |  |  |  |  |  |  |  |  |  |  |  |
| HC, MUAC2 |  |  |  |  |  |  |  |  |  |  |  |  |
| Lung function testing |  |  |  |  |  |  |  |  |  |  |  |  |
| T-cell subsets |  |  |  |  |  |  |  |  |  |  |  |  |
| HIV-1 viral load *(1 year post-ART)* |  |  |  |  |  |  |  |  |  |  |  |  |
| Blood sample store3 |  |  |  |  |  |  |  |  |  |  |  |  |
| Psychosocial assessment4 |  |  |  |  |  |  |  |  |  |  |  |  |
| Pubertal Staging5 |  |  |  |  |  |  |  |  |  |  |  |  |
| Adherence assessment |  |  |  |  |  |  |  |  |  |  |  |  |
| Referral for TB investigations (if TB symptoms)6 |  |  |  |  |  |  |  |  |  |  |  |  |

1Clinical & toxicity symptom checklist, hospitalisation, new diagnoses

2HC-head circumference; MUAC- mid-upper arm circumference;

3Blood sample also taken at recruitment

4Knowledge of diagnosis, disclosure to others, schooling, guardianship, family HIV test

5For children aged 9 years or older

6Sputum (expectorated or induced), CXR, stool, urine will be collected as part of a collaborative study to be conducted by [name] (see Appendix 18.10)

## 7.5 Assessment of growth

All assessments of growth will be measured at baseline, before starting ART and at intervals specified in Table 7.1

Weight will be measured on every scheduled and unscheduled clinic visit using digital weight scales. Standing and sitting height (a measure of leg length)72 will be measured at every scheduled visit. Mid-upper arm circumference and head circumference will be measured six-monthly.

Puberty will be assessed annually using Tanner Staging.73 Tanner Staging will only be carried out in children who are ≥9 years. The following aspects of pubertal development will be recorded for males and females:

- Males- Testicular size (measured using a Prader orchidometer), Penile and pubic hair growth
- Females- Breast size and pubic hair growth; age of menarche

The Tanner pubertal stage recorded will be determined by breast development in females and testicular size in males

## 7.6 Assessment of lung function

Lung function will be carried out at baseline, before starting ART and on a six-monthly basis. Assessment will include:

- Spirometry
- Exercise tolerance -6-minute walk (only at baseline)
- Assessment of dyspnoea, using the MRC dyspnoea scale
- Pulse oximetry
- Respiratory rate

## Assessment of adherence

Adherence to ART will be assessed on every scheduled clinic visit, with a detailed assessment of average adherence made through a questionnaire administered to the participants/carer on a three monthly basis. Adherence will be assessed using self / caregiver report.

A brief standardized adherence measurement tool will be used to assess:

1. three day recall
2. pill taking patterns and
3. average monthly adherence estimate with a visual analogue scale

The adherence tool will be adapted from the WHO Generic Tools for Operational Research (WHO and Population Council). Average monthly (from visual analogue scale data) and mean annual adherence (from 3-day recall data) will be calculated. As an exploratory variable, adherence will be categorised using adherence categories such as <84%, 85-94%, and ≥95% representing low, medium, and high adherence.

In addition, pharmacy refill, dose and quantity of drugs dispensed by the clinic will also be documented.

## 7.8 Blood sampling

CD4 T-cell counts will be measured at baseline, at six monthly intervals, before starting ART and three months post-ART. HIV Viral load will be tested at one year post initiation of ART. Additional blood sampling (15mls) will be collected at baseline, at 6 monthly intervals among those who are not on ART. In those who start ART, blood will be taken at 3 months after starting ART and thereafter annually. Samples will be processed to obtain plasma, PBMC and DNA and stored for future immuno-genetic studies (Appendix 18.10).

a

# POST-PITC PREVALENCE SURVEY FOR UNDIAGNOSED HIV INFECTION

After two years of intervention, the prevalence of undiagnosed and diagnosed HIV infection in the 8 to 17 year age-group in the catchment area of intervention clinics will be measured through an HIV prevalence survey in a random selection of dwellings.

## 8.1 Sampling

A random sample of 90 Census Enumeration Areas (CEAs) located in the study suburbs where the study is taking place will be obtained. The list of CEAs will be obtained from the 2012 National Census (available through ZIMSTAT) with each CEA (defined as a as the smallest delimited census area) allocated a geo-code. Army camps, prisons, police, health institutions, educational institutions, hotels, guesthouses, lodges, refugee or squatter camps and other collective groups (such as nomadic, transit, and orphanages, old people’s homes) will be excluded from the sampling frame.

Simple random sampling will then be used to select the sample. The CEA codes will be used as a sampling frame. All households in the selected CEA will be enumerated. All the households in the CEA will be allocated an identification number. The number of households with children aged between 8 to 17 years will be determined. Any household within the selected CEA that has a child aged 8-17years as a household member will be eligible for participation in the prevalence survey. All the children in the selected household will be eligible for recruitment. Each child aged 8-17 years in the eligible household will be allocated a study number.

All households in the selected CEAs will be visited to confirm the exact location in the CEA, drop off information leaflet about the study and pre-book study interview time. The ZENITH survey team will visit the household for the actual interview at the pre-booked time. In the event that there are no children in the household or the household is vacant, the household will not be selected in the study. If the household is selected, the household head will be interviewed to obtain baseline economic and demographic information about the household and also obtain consent to interview the children. If consent is obtained and children are not at home or the appropriate guardian is not available on the day of visit, an appointment will be made and the household visited at the designated or appropriate time. A household will be visited a further two times if the interviewees are not present on the booked appointment time and date. Eligible children in the selected households will be visited twice if not present on the booked appointment. Where it is not possible to interview the household head or the child the reason for this will be recorded.

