## 3.3 Study Design

The study will be conducted in the main PHCs of six suburbs in Southwest Harare. Each participating PHC will offer PITC routinely to 6-15 years olds over a two year period, a well as decentralised HIV care including ART initiation. Thus, children who test HIV-positive through PITC will be offered HIV care at the same PHC. At the end of two years of implementation of PITC, an anonymised HIV prevalence survey of 8-17 years olds from randomly selected dwellings in the suburbs served by the study PHCs will be conducted. The prevalence of *undiagnosed* HIV infection in the community following two years of PITC will provide an indication of the effectiveness of primary-care based routine HIV testing in providing high enough coverage of HIV diagnosis in this age-group (>80% of children diagnosed). The survey will also provide data on overall HIV prevalence by age in the considered age-group.

Children who test HIV-positive through PITC at the PHCs and reside in the study suburb where the clinic is located will be recruited into a trial of a VLW-delivered intervention to support to households of HIV-infected children aged 6-15 years. Stratified sampling will be used with randomisation of participants within clinics (1:1) to either a) primary care based HIV care or b) primary care-based HIV care plus treatment support provided by VLWs.

The intervention will be delivered over an eighteen month period, with formative work carried out to inform the design of the intervention. This will consist of qualitative interviews with care-givers of HIV-positive children attending for HIV care and health care providers (nurses, doctors, counsellors and pharmacists) at Harare Central Hospital as well as Community-based Organizations to understand the needs of households with HIV-infected children.

Children testing HIV positive at the PHCs including those recruited into the trial, will be recruited into a clinical cohort study. Data from routine clinic visit (including height, weight, clinical symptoms, incident clinical events and adherence) will be collected. In addition, detailed growth monitoring, lung function testing and a psychosocial assessment (i.e. schooling, guardianship, and disclosure) will be carried out at pre-defined intervals. The HIV care cohort will also provide a platform for immunological studies of slow-progression of HIV infection.

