## 8.2 Participants

Eligibility criteria:

- Age ≥8 (day of their 8th birthday or older) to 17 years (one day before their 18th birthday). This age-group has been selected to ensure participants have had complete (2 year) exposure to the PITC intervention
- Written informed consent from the guardian
- Assent from the child

If there is more than one child in the household in the eligible age-range then all the children in the household will be tested. Inclusion of all children in the eligible age-group will provide an estimate of prevalence of HIV among siblings and allow exploration of “clustering” of HIV among children in households.

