## 8.3 Collection of data and biological samples

The selected households will be visited and anonymised HIV testing will carried out on all children resident in the households, with guardian consent and participant assent.

An oral mucosal transudate (OMT) test will be collected from all participants to test for HIV antibodies. Participants will also be asked to provide a urine sample or dried blood spot (DBS) sample to test for antiretroviral drug concentration. This will identify those individuals who may under-report their HIV status.

Each household will be allocated an anonymous identification number and one form will be completed per household with provision for more than one child per household with separate HIV testing numbers identification numbers which are linked to the household per child. A questionnaire will be administered for each household whereby information on the following will be collected:-

- Demographics information on the household:
- The numbers and ages of all children of the household
- Socioeconomic variables, including difficulties in providing food, or in finding money to go to clinic if anyone in the household gets sick
- Demographic information on each child who participates:
- Age
- Sex
- Orphanhood status
- Grade in school (or not attending school and reason)
- Absenteeism from school due to illness
- History of HIV testing (including date of, place of and reason for test) and whether accessing HIV care/on ART

Risk factors for HIV infection at household level will be identified. If consent is declined or there is no guardian available in an eligible household to provide consent to participate, demographic information about the household will be requested from a key informant. This information will be used to define likely HIV status of children through imputation.

Undiagnosed and untreated HIV infection will be defined through self-reported past HIV-testing episodes, and self-reported chronic care medication (specifically, any ART, cotrimoxazole and IPT) being received at the time of interview. Clinical patient held records and any documentation of previous HIV test will be used to confirm the information given.

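### The age band cannot by itself ensure two-year PITC exposure in the survey: no minimum residence is set and length of residence is not among the listed data items, so the undiagnosed share is hard to read as PITC effectiveness

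*Protocol*

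**What the plan says.** Protocol 8.1 draws 90 census enumeration areas by simple random sampling and lists every household in them. The household rule is "Any household within the selected CEA that has a child aged 8-17years as a household member will be eligible for participation". Section 8.2 adds three conditions for the child: age, guardian consent and child assent. The age condition is "Age ≥8 (day of their 8th birthday or older) to 17 years (one day before their 18th birthday", and the reason given for it is "This age-group has been selected to ensure participants have had complete (2 year) exposure to the PITC intervention".

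Section 8.3 states who is tested: "anonymised HIV testing will carried out on all children resident in the households, with guardian consent and participant assent". Under the line "Demographic information on each child who participates" it lists age, sex, orphanhood, school grade, absenteeism through illness, and "History of HIV testing (including date of, place of and reason for test) and whether accessing HIV care/on ART". The household items are composition and socioeconomic variables. Neither list contains length of residence, date of arrival or previous suburb.

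Section 9.2.3 counts all HIV-positive participants who were previously undiagnosed, with no split by residence. Section 3.3 then takes the result as an indication of whether primary-care testing gives "high enough coverage of HIV diagnosis in this age-group (>80% of children diagnosed").

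**The concern.** A child who moved into a study suburb near the end of the two years meets every eligibility condition and is counted in full, yet had little or no chance to be offered a test at the study clinics. The hypothesis in 3.1 supposes that nearly every infected child has at least one clinic consultation during the two years, which presupposes that the child was there.

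The listed data would not let the analyst separate the groups afterwards. Date and place of a past test are informative only for children who have been tested. They cannot tell an undiagnosed newcomer from an undiagnosed long-term resident, and that is the distinction needed.

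The interpretation of the PITC component is at stake. Section 11.1 says no survey before PITC is possible, so the judgement rests on this one cross-sectional estimate. If it shows more than 20% undiagnosed, the reader cannot tell whether PITC missed children it had two years to reach or whether newly arrived children are adding to the undiagnosed.

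**Working it through.** **Plan's own figure.** The protocol states no figure for residence or migration, so there is none to reproduce on that point. The one related figure is the precision in 11.2.2: about 118 infected children and an interval of roughly 40%-60% around 50%. Check: 1.96 × √(0.5 × 0.5 / 118) = 9.0 points, giving 41%-59%, which agrees.

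**Inputs**
- Benchmark: >80% diagnosed, so 20% undiagnosed at the boundary (3.3).
- Undiagnosed share before PITC: 80% (11.1). This is used as the upper value for in-migrants.
- A lower value for in-migrants of 50% undiagnosed (assumption), because some will have had partial exposure or a diagnosis elsewhere.
- In-migrant share *m* of infected children aged 8-17: not in the protocol; assumed 5%, 10%, 20% and 30%.
- Infected children in the survey: 118 (11.2.2).

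**Mixture.** Observed share = (1 − *m*) × u_res + *m* × u_mig, so the shift from the resident value is *m* × (u_mig − u_res).

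Residents at the 20% benchmark:

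| *m* | in-migrants 80% undiagnosed | in-migrants 50% undiagnosed |
|---|---|---|
| 5% | 0.95 × 20 + 0.05 × 80 = 23% | 21.5% |
| 10% | 26% | 23% |
| 20% | 32% | 26% |
| 30% | 38% | 29% |

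The shift runs from 1.5 to 18 points.

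Residents at the 50% used for planning in 11.2.2, in-migrants at 80%: 51.5%, 53%, 56% and 59% for the same shares, a shift of 1.5 to 9 points.

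**Against sampling error.** At 20% with 118 infected: 1.96 × √(0.2 × 0.8 / 118) = 7.2 points, before any allowance for clustering by enumeration area or household. The shift exceeds this when *m* is above 7.2/60 = 12% (in-migrants at 80%) or above 7.2/30 = 24% (in-migrants at 50%). Below those shares it lies inside the sampling error but does not shrink with sample size.

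**Precision of a resident-only estimate.** If 20% are in-migrants, 118 × 0.8 = 94 infected remain, and the half-width at 20% is 1.96 × √(0.2 × 0.8 / 94.4) = 8.1 points.

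**The case against.** Several points on the other side stand.

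- **The target is a community quantity.** Aim 2 in 1.2, the outcome in 3.4.1 and the opening of section 8 all concern undiagnosed infection in the community or catchment. Current residents, newcomers included, are the right population for that. If in-migration keeps coverage below 80%, clinic-based testing is not delivering the coverage sought, and community testing may still be worth considering. A reader might infer that the survey would lead to a wrong decision on community-level testing. The protocol does not support that.
- **The forms are not shown.** Sections 8.3 and 10.2 place the survey forms in appendices. Section 8.3 lists topics, so a residence question may already exist. It cannot be said that the gap is beyond repair in analysis.
- **The statement in 8.2 is attached to the age condition.** It plausibly explains only why the 6-15 band was moved up by two years. That softens the statement but does not make it true, since it claims to ensure complete exposure.
- **Not every in-migrant was unexposed.** Only those arriving at or after the end of PITC had none. Earlier arrivals had part of the period, and one consultation may be enough. Some will have been diagnosed elsewhere, which shrinks the shift and could reverse it.
- **Evidence on mobility is thin.** The remark in 2.3 about guardians concerns consent to testing. It does not show that infected children change suburb often.

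A reader might also take the 18-point shift, 2.5 times the half-width, as the expected bias. It is the extreme corner of an assumed range. At the 50% planning value, even 30% in-migrants at 80% undiagnosed gives 59%, about the edge of the interval that the plan already accepts.

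**Conclusion.** The point holds as a mismatch between a stated property of the survey population and what its design secures. Age and current membership do not ensure two years of exposure, and the data items listed in the protocol would not show who had it. The all-children estimate is sound as community coverage. As a measure of how well PITC worked, it is mixed to an unknown degree, and it understates PITC only if newcomers are less often diagnosed than residents.

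The size cannot be derived from the protocol. Under the assumed ranges, residents at 20% undiagnosed would appear as 21.5-38%, against a simple-sampling half-width of about 7.2 points. The result rests on the assumed in-migrant share, the assumed 50-80% undiagnosed among in-migrants, and the stated 118 infected. This is a cheap improvement to interpretability. It does not invalidate the survey.

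**What to change.** 1. Check the survey form. If it has no residence item, add one per child: the date the child began living in the current suburb.
2. Reword the statement in 8.2 so that the age band is no longer said to ensure complete exposure.
3. Report two estimates side by side: the undiagnosed share among all surveyed children, as community coverage, and the share among children resident throughout the PITC period, for interpreting PITC effectiveness against >80% diagnosed. The second should not replace the first as the only criterion; that would be a debatable change of estimand.

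The cost is one question per child and a wider interval for the resident estimate: about 8.1 points instead of 7.2 if 20% are in-migrants, both before clustering.
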